### Randomization

Participants who meet the inclusion criteria will be randomly allocated to the intervention or control group, as well as stratified into two groups based on BDI-II scores at baseline (≥14 or <14) [46]. An independent biostatistician will generate a stratified permuted block random table by using SAS (SAS Institute Inc). The stratified permuted-block random table will be password protected and blinded to the researchers, and sent to the CRC by an independent research assistant. The assignment will be conducted by the CRC.

### Statistical Methods

#### Effectiveness of the Intervention

For the primary and secondary outcomes, except for MDEs, a mixed model analysis for repeated measures will be used to test the intervention effect (group × time interactions) for 3- and 6-month follow-ups in the total sample (universal prevention), on an intention-to-treat basis. This model will handle and impute missing data with restricted maximum likelihood estimation assuming missing values at random. Effect sizes (Cohen *d*s) and 95% CIs at 3- and 6-month follow-ups will be calculated among those who complete the baseline and follow-up surveys. For MDEs at the 12-month follow-up, a Cox proportional hazard model will be used to estimate the preventive effect of the intervention program on MDEs. All statistical analyses will be conducted using SPSS Statistics v26.0 (IBM Corp).

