**Methods:**

This study is a two-arm, parallel, randomized controlled trial. Participants (N=1400) will be recruited, and those who meet the inclusion criteria will be randomly allocated to the intervention or control (treatment as usual) group. A 6-week, six-module, internet-based stress management program, SMART-CBT, has been developed that includes machine-guided exercises to help participants acquire CBT skills, and it applies machine learning and deep learning technologies. The intervention group will participate in the program for 10 weeks. The primary outcome, depression, will be measured using the Beck Depression Inventory II at baseline and 3- and 6-month follow-ups. A mixed model repeated measures analysis will be used to test the intervention effect (group × time interactions) in the total sample (universal prevention) on an intention-to-treat basis.

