## Methods

### Trial Design

The study will be a nonblinded, parallel, two-arm RCT with a single intervention group that will receive the SMART-CBT intervention and a control group that will receive TAU. The allocation ratio of the intervention group to the control group is 1 to 1. Participants will be randomly allocated to either the intervention group or the control group after they have completed a baseline online questionnaire. Follow-up surveys will be conducted at 3, 6, and 12 months after the baseline measurement, using online questionnaires. The study protocol has been registered at the UMIN Clinical Trials Registry (UMIN-CTR; ID UMIN000043897). This protocol manuscript has been reported according to the SPIRIT (Standard Protocol Items: Recommendations for Interventional Trials) guideline checklist [19].

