### Procedure

Participants will be recruited from a pool of 300,000 people living in all 47 prefectures of Japan who registered with an online survey company. A clinical research coordinator (CRC) from the survey company will send an invitation to this population, with a description of the study’s aim and procedure, and obtain online informed consent to participate in the study. We will recruit 1600 participants in total, including 200 males and 200 females in each of four age groups (20-29, 30-39, 40-49, and 50-60 years old). The CRC will ask those who agree to participate in the study to complete an online questionnaire for the baseline survey. We expect that at least 1400 individuals will be eligible based on the inclusion and exclusion criteria. These participants will be randomly allocated to either the intervention group (n=700) or the control group (n=700). Participants in the intervention group will be asked to use the intervention program for 6 weeks after the baseline survey, and they will be encouraged to revisit and review the program for an additional 4 weeks. Participants in the control group will be given a chance to receive the intervention program upon completion of the study. The participants in the intervention group will be given a token equivalent to JPY 1000 (USD 9.1) if they complete all modules of the program. The participants in the control group will be given a token equivalent to JPY 100 (USD 0.91). Participants in both groups will be given a token equivalent to JPY 30 (USD 0.27) for completing each of the surveys (baseline, and 3-, 6-, and 12-month follow-up surveys).

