### Sample Size Calculation

The required sample size was calculated for one of the outcome variables, ie, depressive symptoms assessed by BDI-II. Previous meta-analyses of web-based universal prevention psychological interventions for improving depression and anxiety in the workplace yielded a summary effect size of 0.25 [8]; our previous study of a guided universal prevention iCBT program among workers reported a smaller effect size on depression (*d*=0.16) at a 6-month follow-up [18]. To detect a minimal effect size of 0.15 at an alpha of .05 and a power of 0.80, the estimated sample size is 699 participants in each group. The statistical power was calculated using the G*Power 3 program [54].

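### The group × time contrast for BDI-II is valid but, read conventionally, less precise than a baseline-adjusted contrast that the same data would allow

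*Protocol article*

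**What the plan says.** Under Effectiveness of the Intervention, the article states that "a mixed model analysis for repeated measures will be used to test the intervention effect (group × time interactions) for 3- and 6-month follow-ups". This applies to all participants, by intention to treat. The section names no covariate, no stratum term and no constraint on the baseline means. On missing data it says: "This model will handle and impute missing data with restricted maximum likelihood estimation assuming missing values at random".

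The abstract says that depression "will be measured using the Beck Depression Inventory II at baseline and 3- and 6-month follow-ups", and Table 2 agrees. Trial Design places the baseline questionnaire before randomisation. Under Randomization, participants are "stratified into two groups based on BDI-II scores at baseline (≥14 or <14").

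The sample size rests on a plain two-group comparison of BDI-II, with the requirement given per arm: "To detect a minimal effect size of 0.15 at an alpha of .05 and a power of 0.80, the estimated sample size is 699 participants". Trial Design says "The allocation ratio of the intervention group to the control group is 1 to 1", and Procedure has participants "randomly allocated to either the intervention group (n=700) or the control group (n=700").

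**The concern.** If time covered only 3 and 6 months, a group × time interaction would test whether the effect differs between those two visits, not whether there is an effect. So baseline has to be one of the repeated outcomes. In the usual model, with a group main effect, each interaction term is then the between-group difference in change from baseline.

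A change contrast corrects chance baseline imbalance with a fixed slope of 1. The best slope is the one estimated from the data, and it is below 1 whenever ρ is below 1 and the variances are equal. Because baseline is measured before randomisation, the two arms have equal expected baseline means by design. A model that uses this gives a smaller standard error from the same participants.

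The stake is power in a trial with little slack: 699 per arm are needed, 700 are planned, and neither Sample Size Calculation nor Procedure mentions an allowance for attrition.

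**Working it through.** **Inputs from the article.** d = 0.15, alpha 0.05, power 0.80 and 699 per group (Sample Size Calculation); 700 per arm (Procedure); 1:1 allocation (Trial Design); stratum cut at BDI-II 14 (Randomization).

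**Assumption.** ρ, the correlation between baseline and follow-up BDI-II, is not given. It is varied below, with equal variances across visits and arms.

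**The plan's own figure.** The normal approximation, n = 2(1.96 + 0.842)²/0.15², gives 698 per arm. The exact two-sided two-sample t-test gives 699 (power 0.8002), as stated. A one-sided test gives 550 and does not match. The calculation uses no baseline correlation.

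**Variance of each contrast, relative to comparing follow-up means alone.**
- Difference in change: 2(1−ρ)
- Baseline-adjusted: 1−ρ²
- Ratio of adjusted to change: (1−ρ)(1+ρ) / [2(1−ρ)] = (1+ρ)/2, a variance reduction of (1−ρ)/2

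Generalised least squares on a three-visit unstructured model (complete data, 700 per arm) gave the same reductions at ρ = 0.4 to 0.7: 30%, 25%, 20% and 15%.

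**Power with no dropout.** Power = Φ(0.15 × √(700/(2v)) − 1.96), where v is the relative variance. At ρ = 0.4:
- change, v = 1.2: 0.15 × √(700/2.4) = 2.56, power 0.73
- adjusted, v = 0.84: 0.15 × √(700/1.68) = 3.06, power 0.87

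| ρ (assumed) | Variance reduction | SE reduction | Power, change | Power, adjusted | n per arm for 80%: change / adjusted |
|---|---|---|---|---|---|
| 0.2 | 40% | 22.5% | 0.60 | 0.82 | 1117 / 670 |
| 0.4 | 30% | 16.3% | 0.73 | 0.87 | 838 / 587 |
| 0.5 | 25% | 13.4% | 0.80 | 0.90 | 698 / 524 |
| 0.6 | 20% | 10.6% | 0.88 | 0.94 | 559 / 447 |
| 0.7 | 15% | 7.8% | 0.95 | 0.98 | 419 / 356 |
| 0.9 | 5% | 2.5% | 1.00 | 1.00 | 140 / 133 |

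**Dropout.** No rate is given. At ρ = 0.5, an assumed 20% loss (560 per arm) gives power of 0.71 against 0.83. An assumed 30% loss (490 per arm) gives 0.65 against 0.77.

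**Effect of the stratified randomisation.** Stratifying on BDI-II already limits baseline imbalance. Let p be the share scoring 14 or more, and assume normal scores. The stratum then explains a fraction f = φ(z)²/[p(1−p)] of the baseline variance, where z is the cut-point. The true relative variance of the change contrast falls to 2(1−ρ) − (1−ρ)²f. With p = 0.3, f = 0.576; at ρ = 0.5 this is 1 − 0.25 × 0.576 = 0.856, and the true loss is 1 − 0.75/0.856 = 12.4%. Over p = 0.2 to 0.4 and ρ = 0.7 to 0.4, the true loss is about 6% to 18%. A model with neither baseline adjustment nor the stratum still reports the larger standard error, and so shows a loss of 15% to 30%.

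**Adding the stratum to the adjusted model.** The stratum is a cut of the baseline score. In a simulation with normal scores and 30% at 14 or above (both assumed), adding it as a constant effect across visits to the equal-baseline-means model raised the variance ratio from 0.75 to 0.86 at ρ = 0.5, and from 0.70 to 0.82 at ρ = 0.4. The constant effect is misspecified, because the gap between strata is largest at baseline. Entered as stratum × visit, it neither harmed nor helped.

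**The case against.** The strongest objection is that the article is silent rather than wrong. It does not say that baseline means are free, and group × time terms are also how the effect appears in a model with a common baseline mean. A condensed article may leave covariates, stratum terms and parameterisation to a full protocol or analysis plan that is not shown. This stands in part: free baseline means are inferred, and the missing stratum term alone would not be a finding. What remains is that the article does name its contrast, and the conventional reading of that contrast is the less precise one.

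Three stronger readings are tempting, and the documents do not support them.
- A reader might infer that baseline BDI-II is left out of the model. It is not: it enters as the first repeated measure. What is not stated is its use as a covariate or through a common baseline mean.
- A reader might infer that the analysis is biased, or invalid because it ignores the stratification. It is neither. Omitting the stratum makes the reported standard error too large, so the test is conservative.
- A reader might take a 15% to 30% loss as a property of this trial. It requires ρ between 0.7 and 0.4, and no ρ is given. Nor is there a retention figure: the 68% under Module 1 Exercise is the response rate of a separate survey.

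It is also fair to say that at ρ of 0.5 or more, with no dropout, the change contrast still reaches the planned 80% power.

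**Conclusion.** The point holds as one of efficiency. On the conventional reading, the planned contrast is a valid difference in change, and for any ρ below 1 it is less precise than a baseline-adjusted contrast. The reduction available in reported variance is (1−ρ)/2; for ρ of 0.7 to 0.4 this is about 8% to 16% of the standard error. Part of the true loss is already recovered by the stratified randomisation, but the reported standard error would not show it. The practical consequence is largest if ρ is below 0.5 or if participants are lost to follow-up, since adjustment may then decide whether 80% power is reached. These sizes rest on an assumed ρ and equal variances; the dropout and stratification figures need the further assumptions stated with them.

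**What to change.** State that the primary effect is the group difference in BDI-II at 3 and at 6 months, from one of two models:

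- **(a)** a repeated-measures model of baseline, 3 and 6 months, with baseline means constrained equal across arms. If the stratum is included, enter it only as stratum × visit.
- **(b)** a model of the 3- and 6-month visits, with baseline BDI-II × visit as covariate plus the BDI-II ≥14/<14 stratum.

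Adjust K6, fear of COVID-19 and absence days for their own baseline value plus the stratum. In the Cox model for major depressive episodes, include the BDI-II stratum or stratify by it.

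The cost is a few sentences of analysis wording and no new data. Option (b) has a small downside: participants with no follow-up contribute nothing to the estimate, which (a) avoids. Once continuous baseline BDI-II is adjusted for, the stratum adds essentially no precision; in (b) it serves to match the analysis to the randomisation.

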#### Subgroup Analysis

The effectiveness of the program may be greater for participants with depression at baseline. We will conduct similar mixed model analyses for the effectiveness of the program among a subgroup of symptoms of depression at baseline (with a BDI-II score of ≥14; indicated prevention).

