### Objectives

To address these unresolved issues, our randomized controlled trial (RCT) aims at investigating the effectiveness of a fully automated machine-guided iCBT program supported by artificial intelligence (AI) technologies, called “SMART-CBT,” for subthreshold symptoms of depression (the primary outcome) at 3- and 6-month follow-ups and for secondary outcomes (psychological distress, fear of COVID-19, and sick leave days at 3- and 6-month follow-ups, and major depressive episodes [MDEs] over a 12-month period) compared to treatment as usual (TAU). Participants will be healthy workers selected from the general working population (universal prevention). We hypothesize that this fully automated machine-guided program will improve the symptoms of depression compared with the control group, with an equal or greater effect size as in previous guided web-based psychological interventions at the 6-month follow-up (0.16-0.25) [8,18] in the total sample (universal prevention). We will also investigate the effect on depression among participants with subthreshold depression (indicated intervention).

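### The subgroup analysis is motivated by a possibly greater effect at baseline BDI-II ≥14, but the only model named is fitted within that subgroup and cannot show or refute a greater effect.

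*Protocol article*

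**What the plan says.** The Subgroup Analysis section has two sentences. The first gives the reason: "The effectiveness of the program may be greater for participants with depression at baseline". The second names the analysis: "We will conduct similar mixed model analyses for the effectiveness of the program among a subgroup of symptoms of depression at baseline", the subgroup being those "with a BDI-II score of ≥14; indicated prevention".

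The model to be repeated is the one under Effectiveness of the Intervention, where "a mixed model analysis for repeated measures will be used to test the intervention effect (group × time interactions" at 3 and 6 months. It contains no stratum term.

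The Objectives section words the subgroup aim without a comparison: "We will also investigate the effect on depression among participants with subthreshold depression (indicated intervention".

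Under Randomization, allocation is stratified on the same BDI-II cut-off of 14, so the factor needed for a comparison already exists in the design.

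**The concern.** The reason given for the analysis is comparative and the analysis is not. A group × time test among participants with BDI-II ≥14 asks whether the effect there differs from zero. It does not ask whether the effect exceeds that in participants below 14. The section names no estimate for the lower stratum and no estimate of the difference.

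A significant result at ≥14 would therefore be no evidence of a greater effect. A non-significant one would be no evidence against it, because the subgroup is only part of a sample sized for the whole. What is at stake is how the result is read. The Background section cites larger effects for indicated than for universal interventions (g=0.52 and 0.25), so readers will set the ≥14 result beside the overall one and draw a comparison that the named analysis cannot carry.

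**Working it through.** **Inputs**
- From Sample Size Calculation: d=0.15, alpha .05, power 0.80, 699 per group.
- From Procedure: 700 per arm.
- From Background: g=0.52 (indicated) and 0.25 (universal), a gap of 0.27.
- Assumed: the share with BDI-II ≥14, which the protocol does not give. I use 20-30% and show 15-50% as the wider range.
- Also assumed: no dropout, SD=1 in both strata, and an unadjusted two-group standard error.

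**1. The plan's own figure.** n = 2(1.960+0.842)²/0.15² = 698 per group by the normal approximation. The noncentral t calculation gives 699, so the stated figure reproduces. A one-sided test would give 550, so the plan is two-sided.

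**2. Chance of a significant subgroup when the strata do not differ.** Let n₁ be the number per arm with BDI-II ≥14. Then SE₁ = √(2/n₁), and the probability is Φ(d/SE₁ − 1.96) + Φ(−d/SE₁ − 1.96). The true effect d is the same in both strata.

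| Share ≥14 | n₁ per arm | SE₁ | d=0.15 | d=0.25 |
|---|---|---|---|---|
| 15% | 105 | 0.138 | 0.19 | 0.44 |
| 20% | 140 | 0.120 | 0.24 | 0.55 |
| 25% | 175 | 0.107 | 0.29 | 0.65 |
| 30% | 210 | 0.098 | 0.34 | 0.73 |
| 50% | 350 | 0.076 | 0.51 | 0.91 |

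Each of these would be a positive subgroup result with no difference between strata. A correctly specified interaction test would be positive in 5%.

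The column for d=0.15 is also the power of the subgroup test at the planning effect: 0.24-0.34 at a 20-30% share, against 0.80 in the total sample. This is why a null subgroup result says little about a smaller effect.

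**3. What the interaction could detect.** With n₀ = 700 − n₁ per arm below 14, SE of the difference = √(2/n₁ + 2/n₀). The difference detectable with 80% power is 2.8016 times that.
- 20%: √(2/140 + 2/560) = 0.134, giving 0.37 SD
- 25%: √(2/175 + 2/525) = 0.123, giving 0.35 SD
- 30%: √(2/210 + 2/490) = 0.117, giving 0.33 SD
- Wider range: 0.42 SD at 15%, 0.30 SD at 50%

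For a difference of 0.27, interaction power is 0.52 at 20%, 0.59 at 25% and 0.64 at 30% (0.44 at 15%, 0.71 at 50%). The 0.27 is a gap between types of intervention in the cited literature, not between strata of one trial, so it serves only as a yardstick.

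**4. Sensitivity to the standard error.** The mixed model uses the baseline score. If the baseline to follow-up correlation were 0.7 (assumed), a change-score SE would shrink by √(2(1−0.7)) = √0.6 = 0.775. At a 30% share, d/SE₁ becomes 0.15/(0.0976×0.775) = 1.98, and the probability in step 2 rises from 0.34 to about 0.51. Greater precision makes a significant subgroup without any difference more likely, not less.

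**The case against.** The strongest reply is that the protocol never claims the program works better in this subgroup. The sentence is tentative, it serves as rationale, and no rule says that significance at ≥14 will be read as a greater effect. The formal aim in Objectives is the effect within the indicated subgroup, and a randomised comparison within a randomisation stratum answers that directly, with no interaction term. All of this stands, and it limits the point to the inference about a greater effect.

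A reader might also infer that only an exaggerated estimate can reach significance in the subgroup, or that a significant subgroup must look larger than 0.15. The documents do not support either as a general statement. At a 20-30% share the critical observed d is 1.96×SE₁ = 0.23-0.19, above 0.15. At a 50% share it is 1.96×√(2/350) = 0.148, below 0.15, and the same value results at a 30% share with the smaller SE of step 4. If the true subgroup effect were near the cited g=0.52, power would be about 0.99 or more at a 20-30% share and no exaggeration would be needed.

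A further reply is that a journal article need not list interaction terms or complementary strata. That would answer a complaint about silence. Here the section names its analysis, and that analysis does not address the reason given for it.

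Finally, the interaction test is weak. It is, but a wide interval on the difference shows the uncertainty that a within-subgroup p-value hides.

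**Conclusion.** The point holds in limited form. The Subgroup Analysis section gives a comparative reason and fixes a non-comparative analysis. The named model serves the aim in Objectives but can neither support nor refute a greater effect at BDI-II ≥14. This does not depend on the size of the subgroup.

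The illustration does. With d=0.15 in both strata, a 20-30% share, no dropout and an unadjusted SE, about 24-34% of trials would show a significant subgroup with no difference between strata. Over shares of 15-50% the range is 19-51%.

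The protocol should not be read as asserting a greater effect or as having a decision rule for one. The primary analysis in the total sample is unaffected. The change is worth making because it is nearly free and prevents a misreading.

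**What to change.** Keep the within-subgroup estimate for the indicated-prevention aim. Then take one of two routes.

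1. **Compare the strata.** In the total-sample mixed model, add the group × time × stratum term (≥14 / <14, as used for randomisation) with its lower-order terms. Report the 6-month effect with 95% CI in each stratum, and the difference with its CI. Give the difference in BDI-II points as well as in SD units, since strata defined by score range may have different SDs. Base any statement of a greater effect only on that difference, and label it exploratory.
2. **Drop the comparison.** Delete the sentence saying that the effect may be greater, and claim only the effect within the subgroup.

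The first route costs a few model terms and a short table, with no extra participants or data. Its drawback is low power: at a 20-30% share only differences of about 0.33-0.37 SD are detectable with 80% power, so the result may be inconclusive and should be reported as such. The second route costs one sentence.

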### Data Monitoring

A data and safety monitoring board will consist of a chair and two members, independent of the research team. The board will meet every 3 months after the first participants are randomized. The purpose of the meetings will be to review the report prepared by the CRC to monitor recruitment progress and data collection.

